## Abstract

**Introduction:** School environments can influence students' dietary habits. Hence, implementing a healthy canteen intervention programme in schools is a recommended strategy to improve students' dietary intake. This study will evaluate the feasibility of providing healthier food and beverage options in selected secondary schools in Malaysia by working with canteen vendors. It also will assess the changes in food choices before and after the intervention.

**Methods:** A feasibility cluster randomised controlled study will be conducted in six secondary schools (intervention, *n* = 4; control, *n* = 2) comprising of rural and urban schools located in Selangor and Perak states in Malaysia. Four weeks of intervention will be conducted among Malaysian adolescents aged 15 years old. Two interventions are proposed that will focus on providing healthier food options in the canteen and convenience shops in the selected schools. Interventions 1 and 2 will entail training the canteen and school convenience shop operators. Intervention 2 will be applied to subsidise the cost of low energy-dense *kuih* (traditional cake), vegetables, and fruits. The control group will continue to sell the usual food. Trained dietitians will audit the canteen menu and food items sold by the school canteen and convenience shops in all schools. Anthropometric measurements, blood pressure and dietary assessment will be collected at baseline and at the end of 4-week intervention. Focus group discussions with students and in-depth interviews with headmasters, teachers, and school canteen operators will be conducted post-intervention to explore intervention acceptability. Under this Healthy School Canteen programme, school canteens will be prohibited from selling “red flag” foods. This refers to foods which are energy-dense and not nutritious, such as confectionery and deep-fried foods. They will also be prohibited from selling soft drinks, which are sugar-rich. Instead, the canteens will be encouraged to sell “green flag” food and drinks, such as fruits and vegetables.

**Conclusion:** It is anticipated that this feasibility study can provide a framework for the conception and implementation of nutritional interventions in a future definitive trial at the school canteens in Malaysia.

## Introduction

There is a concern about the growing prevalence of obesity and unhealthy eating habits among adolescents (1, 2). Obesity and unhealthy diets are associated with chronic diseases, such as cardiovascular disease (3, 4). Promoting healthy eating among adolescents has become an important public health and research priority because the incidence of obesity and overweight among adolescents continues to increase and tends to persist into adulthood (5, 6). Skipping breakfast and high consumption of energy-packed foods are considered among risk factors that lead to overweight and obesity in adolescents (7, 8). A National Health and Morbidity Survey (NHMS) reported that, among Malaysians aged 10–17, the prevalence of obesity had risen from 5.7% in 2011 to 11.9% in 2015 (9–11).

An unhealthy diet contributes significantly to weight gain and obesity. Studies have shown that the quality of the diet declines when children enter adolescence (12). The consumption of fruit, vegetables, and milk decrease, while the intake of sugar-sweetened beverages and confectionery increases through adolescence and early adulthood (13). Fruits and vegetables are key foods that will reduce fat, energy density and increase fibre that are related to lower cardiovascular disease risk in adolescents (14). A cohort study in the UK revealed that childhood dietary habits, namely low fibre intake and consumption of high fat and energy-dense food, are linked to increased adiposity in adolescence (15). Therefore, a healthy diet can lower the risk of obesity among younger people (15). A longitudinal study (MyHeARTs) in Malaysia suggested that students who live in rural areas consumed more sugar, cholesterol, and energy compared with their peers in urban schools (16). Several observational studies (16, 17) have been conducted to understand the dietary patterns among Malaysian adolescents. The findings show that Malaysian adolescents are prone to consume unhealthy foods (18), and have unhealthy eating behaviours (19). The current available data on school-based interventions are not culturally relevant to schools and students in Malaysia. Thus, it is important to design a dietary intervention programme that is evidence-based and culturally relevant for Malaysian adolescents and can be delivered and evaluated in the Malaysian setting. Malaysian foods are influenced by the preparation methods that differ across the Malay, Indian, and Chinese ethnicities. Different ethnic groups have different cuisines and variety of food preparation methods. This leads to different food preferences and eating habits among the ethnicities in Malaysia. Hence, it is important to incorporate cultural differences into designing dietary interventions for better acceptance of healthy foods among school-going adolescents.

Adolescents' dietary behaviour is likely to be strongly influenced by environmental factors (20, 21). The school food environment is often considered as a target for nutritional intervention as school children consumed ~40% of their daily dietary intake at schools (22). Two promising school food environment policies have been introduced by providing fresh fruits and vegetables (F&V) in addition to restricting the sale of sugar-sweetened beverages (SSBs) (23–26). It has been shown that a higher intake of F&V and reduced consumption of SSBs (sodas, sports, and energy drinks) may be beneficial for children by reducing the incidence of cardiometabolic disease (27). Previous interventions conducted in schools in Norway, the Netherlands and US have tried to provide free or subsidised fresh fruits and vegetables, usually as snacks in addition to school meals (28–30).

Interventions targeting the consumption of beverages is essential as many Malaysian adolescents consume large amounts of SSBs, milk, coffee, cordials, and fruit-flavoured drinks with added sugars (31). An 18-month trial among 641 normal-weight children in the Netherlands revealed that replacing SSBs with zero-calorie beverages decreased weight gain and fat accumulation in normal-weight children. This suggests that reducing SSBs intake can cause an impact on body weight in children (32). A systematic review indicated that school-based education programmes focusing on the reduction of SSBs intake with follow-up modules could provide chances for conducting effective and sustainable interventions (33). In addition, by modifying the school environment (e.g., providing water and reorganization of beverages by promoting less SSBs) and having peer-support group to promote health educational programmes could improve their effectiveness (33). Home delivery of more proper drinks has a major effect on the reduction of SSBs consumption and related weight loss (33).

Several initiatives have been implemented in Malaysia and across the world to ensure adherence to established nutritional guidelines and standards, healthy canteen policies, and strategies for all foods served in school canteens (34–36). However, the impact of these programmes and their long-term sustainability are unclear. Addressing this gap is particularly important in Malaysia, where the school is an important provider of two main meals (breakfast and lunch) (37). In a recent systematic review about Malaysian adolescents' dietary intake, there was a small difference in dietary patterns according to ethnic diversity, which indicated that Malays had higher SSBs intake and lower diet quality than Chinese and Indian adolescents (21). Furthermore, Malay adolescents preferred Western-based and local-based dietary patterns while Chinese adolescents intended to follow a healthy-based food pattern, which may reflect the effect of socio-cultural diversity on food preferences (21).

In Malaysia, the schoolchildren purchased food from the canteen and *koperasi* (school convenience shop) which are run by the canteen operators and school administration, respectively. The *koperasi* sells mostly energy-dense snacks and beverages. The staple foods usually was sold at the canteen such as noodles, fried rice, nuggets, and fried chicken, energy-dense traditional cakes (e.g., *Rempeyek, Kuih Peneram, Kerepek Ubi Kayu, Kuih Baulu*, etc.), and SSBs.

Environmental interventions are suggested as more likely to be effective in producing behavioural change (38). Evidence from systematic reviews, which mostly comprised studies implemented in the US, indicated that school-based strategies can be effective in cultivating healthy eating habits and food purchasing behaviours among school children (39–41). These reviews found that by widening choices of healthy foods, limit the sales of junk foods, and affordable price of healthy food options may help to increase intake of fruits and vegetables and reduced intake of saturated fat among school children (39–41). Nevertheless, few studies explored the extent to which school canteens implemented promotion and pricing strategies to promote the purchasing of healthy foods and drinks (42). Studies on food environments in schools have concentrated on reporting the accessibility of healthy foods sold in canteens, in school lunch programmes, or sold by using vending machines with limited information on other practices (42–44). Therefore, the purpose of this study is to evaluate the feasibility of delivering a new programme that will promote the availability of healthy food and drink options, especially at school canteens and school convenience shops in Malaysian secondary schools. We also seek to examine the feasibility of collecting data to assess this intervention approach to determine if a larger evaluation is warranted.

### Aims

The general aim of this study is to assess the feasibility of an intervention programme to improve availability of healthy food items at the school canteen and convenience shop and promote healthy eating practices among school students in Malaysia. The study will be conducted in cooperation with stakeholders (canteen and school convenience shop operators) in secondary schools. The specific objectives are:

To test the feasibility of providing healthier food options (such as minimising SSBs, more availability of fruits and vegetables) at the school canteen in cooperation with food vendors.To test the feasibility of assessing changes in food choices to healthier options while at school among adolescents pre- and post-intervention.To test the feasibility of assessing changes in anthropometric measurements of adolescents, pre- and post-intervention.

## Methods

### Overview of Study Methodology

This study is part of the MyHeARTBEaT project (IF017-2017) approved by Research Ethics Committee at the University of Malaya Medical Centre (MREC ID NO: 2018214-6029). The study was registered at the ISRCTN registry: ISRCTN 89649533. The trial design is a three-arm, parallel-group, un-blinded, feasibility cluster randomized controlled study undertaken within six schools in Selangor and Perak states in Malaysia. It will compare two intervention arms (1 and 2) against a usual practice control conducted in six secondary schools, of which four schools will receive the interventions and two will serve as controls. Two interventions are proposed which will focus on providing healthier food options available for sale at the school canteen and convenience shops in the selected schools. Intervention 1 will entail training the canteen and school convenience shop operators to prepare healthier food options in the canteen. The research team will train food operators on the benefits of selling healthy food. Intervention 2 also will create awareness, with the cooperation of food vendor operators among students on consuming healthy food. It will include subsidising the price of vegetables, fruits, and low energy-dense *kuih* (traditional cake). The training of the canteen and school convenience shop operators will follow intervention (1) and focus on training the staff who will sell subsidised fruits, vegetables, and low-energy *kuih*. The control group will continue to sell the usual food.

Trained dietitians will audit the canteen menu and food items sold by the school canteen and convenience shops in all schools (during the 4-week intervention phase, once a week). The menu audit process has been implemented in other studies (45). The study outcome measures will be assessed at the individual level and will consist of a 3-day diet history assessment and anthropometric measurements that will be conducted at baseline and post-intervention (4 weeks after intervention). Focus group discussions with students who will be involved in the intervention and interviews with teachers, school headmasters, and canteen operators will be conducted post-intervention to explore the acceptability and barriers in implementing the proposed intervention (see Supplementary Material 1). Estimation of sales will be done based on weekly receipts from the canteen and school convenience shop operators of healthy food items, such as vegetables, fruits, and low-calorie *kuih*. The data will be collected at baseline (August to September 2018) and the following intervention will be carried out after 3 months the year after (January to April). The summary of intervention assessment and logic model are shown in Figures 1, 2, respectively.

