➢ Training: Canteen and school convenience shop operators will have to provide healthy food options and consider alternative methods of cooking by using the Training Manual developed based on the Malaysian Healthy Canteen Guideline (52). A trained dietitian who is the main investigator of this study (HM) will deliver the training in these two schools, and the canteens will be assessed each week on the foods they sell.➢ Fruits, vegetables, and low energy-dense (low ED) *kuih* (traditional cakes) will be subsidised. The canteen operators in this group of interventions will receive a weekly allowance (the amount will be modified when necessary) to sell fruit, vegetables, and low ED *kuih* (e.g., *Ketayap, Cakoi, Cucur cempedak, Apam*) at subsidised prices.➢ All students (Form three students) will receive (Ringgit Malaysia RM 2) coupons that subsidise the price of fruits (will provide 2 days weekly over 4 weeks) and low ED *kuih* (given 2 days weekly over 4 weeks). Therefore, the total value of coupons per week for one student will be RM 4. This coupon will be given to the students weekly. When they buy fruit/*kuih*, the coupon will be placed in a specific box, and the teacher in charge will collect them daily and keep a record of how many coupons have been used as the subsidy.➢ In the subsidised group, schools will be provided with funds to prepare healthy food. This will give them additional money for their weekly purchases to prepare extra vegetables for the study participants. For example, if they purchase vegetables worth 200 Ringgit (RM) per week, they will get 100 Ringgit (RM) subsidy so that they can prepare an extra tray of vegetables per week. The dietitian will visit the school on a weekly basis for evaluation. The receipts of the vegetables will be given to the dietitian, who will monitor them by visiting the school every week to examine the report by the teacher in charge.➢ Providing free drinking water by installing a proper water container/tank to dispense drinking water. The dietitian will check every week whether the water will be filled up during the school period and whether it will be utilised by the students. This will be recorded by the teacher in charge and cross-checked during the weekly visit of the dietitian.

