This school-based study is intended to provide new insights regarding the implementation of healthy foods and drinks environment in Malaysian schools, including distribution of subsidised fruits and vegetables and low ED *kuih* that may improve healthy food intake among Malaysian adolescents. The possible implication of this study includes minimizing the availability of SSBs sold in school canteen in the future. We also want to see the availability of fruits and vegetables at the school canteen and the acceptance of healthier food options among the school adolescents. By offering more of healthier option of foods and beverages in school, it will be good to evaluate if changes toward environment may enable the students for better healthy options. From this healthy canteen and convenience shop interventions, we would like to see any changes on anthropometric measurements within a month of intervention. This will enable us to plan for larger scale study in the future. With all the intervention planned, it is anticipate it should be acceptable as we do take into account the diversity of Malaysian ethnic background.

This study is anticipated to be useful in intervention development process and identifying ways to improve the availability of healthy foods within the school environment and modifying healthy canteen guidelines and policy development. It is expected that the findings from this study can provide a framework for the conception and implementation of nutritional interventions at the school canteens in Malaysia that will be tested for efficacy in a future definitive trial.

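### Baseline lies at least three months before a 4-week intervention and follow-up is worded two ways, so raw pre-post change cannot be read as change over the intervention

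*Protocol article*

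**What the plan says.** The Overview of Study Methodology gives the calendar: "collected at baseline (August to September 2018) and the following intervention will be carried out after 3 months the year after (January to April". For the duration, the Abstract has: "Four weeks of intervention will be conducted among Malaysian adolescents aged 15 years old".

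The follow-up time appears in two forms. In the Abstract, the anthropometric, blood pressure and dietary data "will be collected at baseline and at the end of 4-week intervention". In the Overview of Study Methodology, the diet history and anthropometry are "conducted at baseline and post-intervention (4 weeks after intervention").

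The second and third specific objectives under Aims are to test whether pre-to-post changes in food choices and in anthropometry can be assessed. The Discussion and Conclusion states the hope for the latter: "we would like to see any changes on anthropometric measurements within a month of intervention".

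Three other places bear on the point. Recruitment and Randomisation Procedures hands out the information and consent form one week before the intervention. The section on Intervention 2 runs the coupons over 4 weeks. Planned Analysis rules out any formal comparison between arms and any significance testing, and says effects will be judged by effect size.

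**The concern.** A pre-post difference describes a 4-week intervention only if the two measurements closely bracket those 4 weeks. Here the first measurement is taken months earlier, in the previous calendar year. Whatever happens to a 15-year-old in the meantime is part of the measured change. That matters most for height, weight, waist and body fat, which can shift with elapsed time alone.

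The follow-up wording raises a separate problem. If the second measurement comes 4 weeks after the intervention has ended, the 3-day diet history describes days without coupons. Dietary intake is the basis of the primary outcome envisaged for the larger trial.

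The purpose of the study is at stake. It is meant to show whether change can be assessed, so that a larger trial can be planned. This schedule does not try out the measurement procedure that such a trial would need. It would also yield change scores that are easily misread as the intervention's effect.

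**Working it through.** **Inputs.** Baseline window: 1 August to 30 September 2018. Intervention window: January to April of the year after, read as 1 January to 30 April 2019. Both come from the Overview of Study Methodology, taken at the calendar limits of the stated months. Duration: 28 days (Abstract). One month is taken as 30.4375 days.

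**The plan's own figure.** The shortest gap runs from 30 September 2018 to 1 January 2019: 93 days, and 93 / 30.4375 = 3.06 months. The stated 3 months is reproduced, but only as the minimum.

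**Longest gap.** The latest start that lets 28 days finish by 30 April is 3 April 2019. From 1 August 2018 that is 245 days, and 245 / 30.4375 = 8.0 months. This assumes that both windows are used in full, which the article does not say.

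**Share of the pre-post interval that is exposed** (exposed share = 28 / interval):

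| Follow-up read as | Interval, shortest | Exposed | Interval, longest | Exposed |
|---|---|---|---|---|
| End of the 4 weeks | 93 + 28 = 121 days | 28/121 = 23% | 245 + 28 = 273 days | 28/273 = 10% |
| 4 weeks after the end | 93 + 56 = 149 days | 28/149 = 19% | 245 + 56 = 301 days | 28/301 = 9% |

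So 77% to 91% of the interval is unexposed, across both readings. With baseline immediately before the start, the interval would be 28 days (100% exposed) or 56 days (50% exposed).

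**What this means for a drifting measure.** Assume, for illustration only, that a measure drifts at a constant rate. The drift over the whole interval, relative to 28 days, is then the ratio of the two lengths whatever the rate: 121/28 = 4.3 to 273/28 = 9.8 times for follow-up at the end, and 149/28 = 5.3 to 301/28 = 10.8 times for follow-up 4 weeks later. The documents give no rate, so no amount in kilograms or centimetres can be stated.

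**The two follow-up statements side by side.** The Abstract ties follow-up to the end of the 4 weeks. The Methods place it 4 weeks after intervention. Counted from the start of the intervention, the two agree. Counted from its end, they differ by 28 days, and the second falls after the coupon period.

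**Consent.** Consent forms go out one week before the intervention. With the stated baseline months, that is at least 93 - 7 = 86 days after the last possible baseline measurement. These two statements do not fit together as written.

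**The case against.** The strongest reply is that the trial has randomised control schools. If all arms follow the same calendar, growth and season affect them alike in expectation and cancel when changes are compared between arms. This stands in principle and limits the damage. It does not remove it: there are two schools per arm, no matching of measurement dates is stated, and no formal between-arm comparison is planned.

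A second reply is that this is a feasibility study. The objectives concern whether change can be assessed, not how large it is, and the progression criteria (more than 50% GREEN items, 80% recruitment) do not use pre-post change. The sentence about change within a month is a hope voiced in the Discussion. This lowers the stakes, but the measurement schedule is itself part of what is being tested.

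Third, the follow-up wording may not be a contradiction, since 4 weeks after intervention can be counted from its start. This stands: it is an ambiguity to be settled. Figure 1, the schedule of assessments, is not shown and may settle it; it may also show a second baseline that the text does not mention.

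Several stronger readings are tempting, but the documents do not support them:

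- A reader might infer that the change mainly reflects growth and season. The documents give no growth rate, seasonal pattern or expected effect. Share of time is not share of change, and a diet history measures recent intake, which need not accumulate over months.
- A reader might infer that schools start at different times and that timing lines up with arm. The January-April window could equally hold training, the 4 weeks, follow-up and interviews.
- A reader might infer that the students given coupons ("All students (Form three students) will receive" them) are not those measured at baseline, or that many have already turned 16. The first needs the school year to turn over between the two dates, and the second needs an age distribution. The article gives neither.

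**Conclusion.** The point holds in a limited form. On the printed dates the gap from baseline to start is at least 93 days, and up to about 245 if the windows are fully used. Exposure covers about 10% to 23% of the interval to the end of the intervention, or 9% to 19% if follow-up is 4 weeks later. A raw within-student change therefore mostly spans unexposed time and cannot be presented as change within a month of intervention. This applies most clearly to anthropometry and less to diet. For diet the main risk is the follow-up time, and that risk exists only if the Methods wording counts from the end of the intervention.

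The lower bound of the gap rests only on the stated months. The upper bound rests on full use of both windows. Nothing here depends on a growth rate, staggered starts or a change of school year. The finding is a worthwhile and cheap improvement to the design; it does not invalidate the feasibility study.

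**What to change.** - Take the planned student baseline shortly before the intervention starts, on the same calendar in all three arms (control schools included) and in the same students who will be exposed. Reconcile this with the consent timing in Recruitment and Randomisation Procedures, so that consent precedes measurement. The school characteristics recorded before randomisation need not move.
- Set follow-up in the final intervention week, so that the 3-day diet history falls while the intervention is running. Word this identically in the Abstract and the Overview of Study Methodology, and check Figure 1 against it.
- If only August-September baseline data exist, do not present raw pre-post change as the intervention's change. Report, descriptively, the change in each intervention arm minus the change in the control arm; use BMI-for-age z-scores; and give each school's interval from baseline to start and to follow-up. This needs no significance test and so fits the Planned Analysis. Reword the Discussion sentence about change within a month.

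The cost is tighter scheduling of the existing dietitians and medical officers, who may be needed in several schools within a short period. No visit is added. If baseline is already complete, only the reporting and the wording change.
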